## Abstract

**Background:**

Late-life depression (LLD) affects up to 18% of older adults and has been linked to elevated dementia risk. Mindfulness-based cognitive therapy (MBCT) holds promise for treating symptoms of depression and ameliorating cognitive deficits in older adults. While preliminary findings are promising, a definitive RCT investigating its effects on late life depression and cognition have not yet been conducted. We present a protocol describing a multi-site blinded randomized controlled trial, comparing the effects of MBCT and of an active control, a Health Enhancement Program (HEP), on depressive symptoms, executive functioning, and brain biomarkers of LLD, among several other exploratory outcomes.

**Methods:**

Two-hundred and thirteen (*n* = 213) patients with LLD will be recruited at various centers in Montreal, QC, Canada. Participants will undergo stratified randomization to either MBCT or HEP intervention groups. We will assess changes in (1) depression severity using the Hamilton Depression Rating Scale (HAM-D17), (2) processing speed and executive functioning, (3) brain biomarkers of LLD (hippocampal volume, default network resting-state functional connectivity and executive network resting-state functional connectivity), and (4) other exploratory physiological and mood-based measures, at baseline (0 weeks), post intervention (8 weeks), and 26 weeks after baseline.

**Discussion:**

The proposed study will assess the clinical potential of MBCT to improve symptoms of depression, as well as examine its impact on cognitive impairments and neurobiological markers, and thus inform its use as a promising adjunct in the treatment of LLD.

**Clinical trial registration:**

www.ClinicalTrials.gov, identifier: NCT05366088.

## Background

With a global prevalence between 9 and 18% (Luijendijk et al., 2008), late life depression (LLD) affects over 300,000 new Canadian seniors with $5 billion in direct health-care costs (Vasiliadis et al., 2013). LLD contributes to increased health-care utilization (Vasiliadis et al., 2013; Sivertsen et al., 2015), decreased quality of life (Sivertsen et al., 2015) and caregiver burden (Vasiliadis et al., 2013), and is associated with a 2-fold increased risk of physical comorbidity and mortality (Grover et al., 2018; Wei et al., 2019). An estimated 60% of patients with LLD will be resistant to treatment-as-usual (TAU), antidepressants and psychotherapy (Knochel et al., 2015). Furthermore, Antidepressants are discontinued in 30% of older adults due to tolerability issues (Tham et al., 2016; Lindblad et al., 2019).

Cognitive functioning deficits are found in 20–50% of people with LLD (Koenig et al., 2014a), and cognitive changes remain resistant to treatments in ≥30% of these individuals (Lee et al., 2007; Bhalla et al., 2009). In particular, processing speed and executive function deficits have been associated with poor treatment response (Story et al., 2008; Jungwirth et al., 2011; Pimontel et al., 2012; Cristancho et al., 2018; Rutherford et al., 2021). The most consistently replicated brain biomarkers of LLD are hippocampal atrophy (Du et al., 2014; Taylor et al., 2014) and brain network dysregulation (Tadayonnejad and Ajilore, 2014). This pattern of hippocampal atrophy and altered functional connectivity is linked to elevated dementia risk in LLD (Rashidi-Ranjbar et al., 2020; Schwab et al., 2020).

Mindfulness-based cognitive therapy (MBCT) targets specific brain circuits implicated in memory and attention regulation and holds promise for ameliorating cognitive deficits. Mindfulness interventions have been shown to increase cognitive functioning (Berk et al., 2017) functional connectivity of the default network (Sevinc et al., 2021) and gray matter concentration in the hippocampus in as little as 4-weeks in older adults (Greenberg et al., 2019). Pilot studies have also demonstrated reductions in depressive symptoms following MBCT treatment with medium to large effect sizes, comparable to first-line antidepressants and individual psychotherapy (Barnhofer et al., 2009; MacKenzie and Kocovski, 2016; Torres-Platas et al., 2019; Musa et al., 2020).

While preliminary findings are promising, a definitive RCT investigating its effects on late life depression and cognition has not yet been conducted. This study will compare the effects of MBCT vs. an active control group, Health Enhancement Program (HEP) on symptoms of LLD as well as memory and cognition and brain structure and function.

## Methods

### Study design

A multi-site phase III RCT with 213 LLD patients, randomized 1:1 to MBCT or HEP. This will be an 8-week two-arm, assessor-blind RCT of MBCT vs. HEP in LLD, at various centers in Montreal. Participants will attend three assessment sessions (baseline/0 weeks, 8 weeks, and 26 weeks) in a research-hospital setting. Participants will attend either MBCT or HEP during group sessions for 2 h/week, for 8 weeks. We will assess change in:

Depression scores (HAM-D17) in the MBCT arm compared to HEP at 8 weeks. We will also assess whether participants in the MBCT arm will continue to have reduced depression scores at the 26-week follow-up (Primary outcome).Executive functioning and processing speed in the MBCT arm compared to HEP at 8 weeks. We will also assess whether participants in the MBCT arm will continue to have improved cognitive scores at the 26-week follow-up (Secondary outcome A).Hippocampal volume, default network resting-state functional connectivity and executive network resting-state functional connectivity at 8 weeks. We will also assess whether participants in the MBCT arm will maintain greater increases in hippocampal volume, increases in default network resting-state functional connectivity, and decreases in executive network resting-state functional connectivity at the 26-week follow-up (Secondary outcome B).

### Interventions

Participants will be randomized to Mindfulness-Based Cognitive Therapy (MBCT) or Health Enhancement Program (HEP) for 8-weeks, in addition to their usual antidepressant therapy and/or psychosocial care. MBCT will be delivered by licensed MBCT clinicians, while HEP will be delivered by trained HEP teachers which meet the *Qualifications and Recommended Guidelines for HEP Providers*, outlined in the HEP Guidelines (Sullivan et al., 2011). See Figure 1 for an overview of the allocation of participants and the study timeline.

**Figure 1 F1:**
[figure not shown]
Participant Allocation Flowchart.

#### Mindfulness-based cognitive therapy

MBCT is an 8-week therapy integrating formal mindfulness meditation (e.g., breath and body awareness) and informal mindfulness (e.g., eating, walking). Participants are taught to attend non-judgmentally to present moment experiences. MBCT includes cognitive therapy techniques to target the ruminative thought processes and identification with negative emotions seen in depression (Segal et al., 2002). MBCT teaches participants how to disengage from habitual (“automatic”) dysfunctional cognitive routines, in particular depression-related ruminative thought patterns that perpetuate depressive symptoms and increase vulnerability to relapse (Segal et al., 2018).

The program consists of group sessions 2 h/week, for 8 weeks, and will be adapted to older adults to promote comfort and safety, e.g., decreasing sitting meditation time (max. 20 min) and modifying postures. Brief discussions will reinforce principles of mindfulness: awareness, non-judgment and acceptance. Participants will be provided with meditation recordings to facilitate home practice (~30 min/day, 6 days/week). Interventionists will meet regularly, to harmonize their curriculum/geriatric modifications of MBCT. Fidelity of intervention will be assessed by asking facilitators which elements of MBCT they covered in each session. Additionally, an independent assessor will measure fidelity of intervention by administering the Mindfulness-Based Interventions-Teaching Assessment Criteria (Crane et al., 2013; Evans et al., 2021).

#### Health-enhancement program

HEP teaches health-enhancing techniques and was designed by University of Wisconsin and NIH as a manualized active control group program for mindfulness-based intervention trials (Sullivan et al., 2011; MacCoon et al., 2012). We have tailored HEP to be structurally equivalent to MBCT, with similar-sized groups, meeting weekly for 2 h for 8 weeks, and similar amount of home practice (~30 min/day, 6 days/week). HEP controls for several non-specific factors in mindfulness groups, including: group support/morale, behavioral activation, stigma reduction, facilitator attention, treatment duration, and time spent on home practice. Participants will learn about health promotion, healthy diet, music, and gentle exercise, but not about breathing techniques or meditation.

#### Randomization

Participants will undergo 1:1 simple randomization to the intervention (MBCT) or the active control (HEP), stratified by sex and study site to control for unequal numbers of participants and differential efficacy between sites. Raters and clinicians will be blinded to participant group allocation and participants will be blinded to study hypotheses. We will offer the MBCT and HEP in groups of 8–11 participants recruited on a rolling basis.

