### Statistical analyses

Primary analyses will be based on intent-to-treat, not per-protocol. However, we will additionally conduct sensitivity analyses for those participants who completed at least 75% of intervention sessions.

*Analysis 1*. To assess whether MBCT improves symptoms of LLD and quality of life compared to an active control (HEP) over 8 and 26 week samples, we will build generalized mixed models to test the following hypotheses: *1A*. The MBCT group will have a greater reduction in Hamilton Depression Scale (HAM-D17) scores compared to HEP controls, and *1B*. The MBCT group will maintain these improvements at 26-weeks.

*Analysis 2*. Investigate the impact of MBCT on cognitive deficits in LLD we will analyze the Z-scores at initial, 8-week and 26-week follow-up of MBCT and HEP groups using generalized mixed models to test the following: *2A*. Compared to HEP, MBCT will be associated with greater improvements in executive functioning and processing speed scores, and *2B*. The MBCT group will maintain these improvements at 26-weeks.

*Analysis 3:* The neuroimaging analysis is a pilot that will generate effect size estimates for future definitive studies examining neural mechanisms of MBCT in LLD, including the following: *3A*. MBCT patients will be superior to HEP controls with respect to increases in hippocampal volume, increases in default network resting-state functional connectivity, and decreases in executive network resting-state functional connectivity at 8 weeks, and *3B*. The MBCT group will maintain these changes at 26-weeks.

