#### Power analysis

We estimate a total sample size of 213 participants randomized, with 170 study completers (20% loss to follow-up) based on effect sizes (ES) estimated from our preliminary data and meta-analyses of adult mindfulness-based interventions RCTs. In our preliminary RCT (Torres-Platas et al., 2019), 8-week MBCT was associated with a 7.9 (SD: 4.4) point improvement on PHQ-9 scores vs. TAU 4.0 (SD: 4.7). Cohen's d = (7.9–4.0)/4.55 = 0.86. Two meta-analyses of mindfulness RCTs (*n* = 35 studies (Hofmann et al., 2010) and *n* = 12 studies (Strauss et al., 2014) found ES (Hedge's g) = 0.50 vs. active control, and ES (g) = 0.41–0.64 vs. TAU in adults with depressive symptoms.

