#### Subgroup analyses

We will stratify by sex, gender and site, and reporting outcomes by strata. Sex, along with other baseline characteristics, will also be included as covariates in statistical models to capture their effects on outcomes. We will conduct subgroup analyses on primary outcome (HAM-D depression score) in patients with MCI (MoCA scores 19–25) or normal cognitive functioning (≥26). In addition to site and sex we will describe the following key treatment factors: age, years of education and medical burden. In our *post-hoc* analysis, we will also assess effects, if any, of the following on treatment response: baseline neuroimaging and cognitive biomarkers; anxiety, mindfulness, medication use, ethnicity, socioeconomic status; vascular burden index, age of first depressive episode, and number of lifetime depressive episodes. Because this is a multisite trial, we will fit a site by treatment interaction term to accommodate differential treatment efficacy across sites. We will also stratify smaller and larger groups (8–9 and 10–11) and fit a group size by treatment interaction term to assess differential treatment efficacy among groups of different sizes.

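### Both arms are delivered in therapy groups of 8–11, but the sample size allows for dropout only and the one group term named does not account for within-group correlation

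*Protocol article*

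**What the plan says.** Allocation is at the level of the person (Randomization): "Participants will undergo 1:1 simple randomization to the intervention (MBCT) or the active control (HEP), stratified by sex and study site". Delivery is not. The same section states: "We will offer the MBCT and HEP in groups of 8–11 participants recruited on a rolling basis". The section on the Health Enhancement Program (HEP) gives that arm groups of similar size and the same weekly two-hour schedule over eight weeks. It also lists support and morale within the group, and the facilitator's attention, among the non-specific influences that HEP is meant to balance.

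The Power analysis section says: "We estimate a total sample size of 213 participants randomized, with 170 study completers (20% loss to follow-up". It cites meta-analyses that "found ES (Hedge's g) = 0.50 vs. active control, and ES (g) = 0.41–0.64 vs. TAU in adults with depressive symptoms". It does not state a significance level, a power, which effect size was chosen, a number of groups or an ICC.

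For the depression outcome, Statistical analyses says "we will build generalized mixed models to test the following hypotheses"; the cognitive analysis uses the same class of model. No random effect of any kind is named. Therapy groups appear in a model only under Subgroup analyses, where the authors will "fit a group size by treatment interaction term to assess differential treatment efficacy among groups of different sizes", with groups split into 8–9 and 10–11 members.

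**The concern.** People who spend eight weeks in the same group with the same facilitator tend to have correlated outcomes. The article's own reasons for choosing HEP make this plausible in both arms, because group morale and facilitator attention are shared by everyone in a group. Individual randomization does not remove the correlation, which arises after allocation.

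Two things are at stake. First, with any positive ICC, 170 completers carry less information on the treatment effect than 170 independent people, and the sample size shows no allowance for this. Second, if the model for the Hamilton depression score or the cognitive scores left therapy group out, its standard errors would be too small. The group-size term does not help: a fixed effect for larger versus smaller groups leaves members of any one group as correlated as before. Group size is also a property of the group, so that interaction is a contrast among about 22 groups and not among 213 people.

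**Working it through.** **Inputs from the article.** 213 randomized, 170 completers, 20% loss and g = 0.50 versus active control (Power analysis); 1:1 allocation and groups of 8–11 in both arms (Randomization).

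**Assumptions, because the article gives no figure.** Two-sided 5%; mean group size 9.5, hence 9.5 × 0.8 = 7.6 completers per group; ICC 0.01 to 0.10.

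**Step 1: reproduce the stated size.** 170 / (1 − 0.20) = 212.5, rounded up to 213. Dropout accounts for the whole inflation.

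**Step 2: where 170 could come from.** Per arm, n = 2(z₁ + z₂)² / d².
- d = 0.50, 90% power: 2(1.960 + 1.282)² / 0.25 = 84.06, so 85 per arm and 170 in total.
- d = 0.43, 80% power: 2(1.960 + 0.842)² / 0.1849 = 84.9, also 85 per arm.

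The first uses the article's active-control effect; 0.43 appears nowhere in it. Both are back-calculations under independence. For 85 per arm and d = 0.50, the t-test power is 0.900.

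**Step 3: number of groups.** 213 / 11 = 19.4 and 213 / 8 = 26.6, so about 19 to 27. At 7.6 completers per group, 170 / 7.6 = 22.4 groups, leaving about 20 degrees of freedom for a between-group comparison of two arms.

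**Step 4: effect of clustering.**
- Design effect: DE = 1 + (7.6 − 1) × ICC.
- Effective N = 170 / DE.
- Type I error if group is ignored = 2[1 − Φ(1.96 / √DE)].
- Power: noncentral t with noncentrality 0.50 × √(85 / (2 × DE)).

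| ICC (assumed) | DE | Effective N | Type I error if group is left out | Power, d = 0.50, no df penalty | Power, d = 0.50, about 20 df |
|---|---|---|---|---|---|
| 0.01 | 1.07 | 159 | 5.8% | 88% | 85% |
| 0.02 | 1.13 | 150 | 6.5% | 86% | 83% |
| 0.05 | 1.33 | 128 | 8.9% | 80% | 77% |
| 0.10 | 1.66 | 102 | 12.8% | 71% | 67% |

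Part of the loss in the last column comes from the degrees of freedom alone: at ICC 0, moving from 168 to about 20 takes power from 90% to 87%.

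**Step 5: sensitivity.**
- Group size: with 6.4 to 8.8 completers per group (8 × 0.8 to 11 × 0.8), ICC 0.05 gives a type I error of 8.2% to 9.6% and a cluster-level power of 79.3% down to 74.2%. ICC 0.10 gives 11.4% to 14.2% and 71.3% down to 63.5%.
- Design target: if it was d = 0.43 at 80%, the cluster-level powers at the four ICCs are about 73%, 71%, 64% and 54%. The pattern does not depend on which back-calculation is right.

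**The case against.** The strongest reply concerns what the article leaves open. It says mixed models and names no random effects, not even one for participant, which repeated measurements would need. That is silence about the whole random structure and not a decision to omit therapy group. Such detail is commonly left to a full protocol or analysis plan, and neither is shown. A reader might infer that the primary test is anticonservative. The document does not support that as a fact: it follows only if group is left out and the ICC is positive. This part of the objection stands.

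A reader might also infer that the power is overstated. No power is stated, so none can be overstated; 90% at d = 0.50 is a back-calculation, and other combinations fit the same total. This stands too. What remains is that 170 matches an independence calculation and shows nothing added for groups.

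The size depends on an ICC that the article does not give. At 0.01 the effect is mild: a design effect of 1.07 and a power of 88% before the degrees-of-freedom penalty. The calculation is also unadjusted, whereas the article plans baseline covariates, which could recover some precision. Both are fair, and both argue for a stated range.

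It is not known at what level the group-size interaction will be tested, so one cannot say that it will be tested wrongly. The preliminary d = 0.86, from PHQ-9 scores against usual treatment, is a separate question of evidence and forms no part of this point.

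The reply does not reach the sample size itself. The article sets out its basis, and the arithmetic shows an allowance for dropout only.

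**Conclusion.** The point holds in a limited form and should be fixed. Established from the article: both arms are group-delivered, 213 is exactly the dropout-inflated 170, and the one group term named does not deal with within-group correlation. Any positive ICC then leaves 170 completers with less precision than independence implies. On the assumptions above, cluster-level power at d = 0.50 runs from about 85% at ICC 0.01 to about 67% at ICC 0.10, against 90% under independence.

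The type I error consequence, about 5.8% to 12.8% over the same range, is conditional on therapy group being omitted from the model. The estimated treatment effect is not claimed to be biased. Nor do the documents show that the trial must be enlarged, since no target power is stated against which to call it too small.

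**What to change.** - Record a therapy-group identifier for every participant in both arms.
- In Analyses 1 and 2, specify a random intercept for therapy group nested in arm, with Kenward-Roger or Satterthwaite degrees of freedom. If a full protocol or analysis plan already does so, a sentence in the article saying so is enough.
- Test the group-size-by-treatment interaction against variation between groups.
- Restate the power for 170 completers, giving the chosen effect size, the significance level and an assumed ICC range. At d = 0.50 and ICC 0.05, for example, it would read about 77%.

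These choices should be settled before unblinding, since a later choice would be open to challenge. No extra patients are needed. The cost is one recorded variable, some analysis wording, a less favourable stated power and somewhat wider intervals. Relative to a model that ignores group, standard errors grow by √DE: about 3% at ICC 0.01 (√1.066 = 1.03), 15% at 0.05 (√1.33 = 1.15) and 29% at 0.10 (√1.66 = 1.29).

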### Outcomes

A screening assessment will be conducted to determine a participant's eligibility for the study. Following completion of the informed consent process, baseline assessments will be completed. A medication record will be collected as per participant report along with reconciliation from pharmacy records. Outcomes will be measured at initial, week 8 (primary study endpoint), and at week 26 follow-up stages (maintenance effects). The following scales will be administered at the baseline assessments.

#### Primary outcome

##### Hamilton depression rating scale (HAM-D17) scores

The HAM-D17 is a well-validated assessor-rated scale used in LLD trials (Koenig et al., 2014b; Lavretsky et al., 2015). HAM-D17 includes 17 items, scored 0–4, with a total score of 0–52: Scores ≥24, 17–23, 8–16, and 0–7 indicate severe, moderate, mild, and no depression, respectively.

#### Secondary outcomes

##### Cognitive testing scores

Processing speed [Trail Making Test A (Reitan, 1956) and WAIS-IV Digit Symbol (Wechsler, 2012)] and executive functioning [Trail Making Test B (Reitan, 1956), WAIS- IV Digit Span (Wechsler, 2012), Emotional Stroop Task (Williams et al., 1996), and Verbal Fluency Test (Lezak et al., 2004)] domain Z-scores will be calculated using a neurocognitive battery, conducted by trained assessors, at baseline, 8-weeks and 26-week follow up; and global cognition [exploratory; Montreal Cognitive Assessment (MoCA)] will be calculated at baseline, 8- and 26- week follow-up.

##### Brain biomarkers

Functional and structural magnetic resonance imaging (MRI) will be collected from a subset of the overall sample (*n* = 40) at Montreal sites (McGill and UdeM) at baseline, 8-weeks, and 26-weeks in a 3T Siemens Prisma scanner. All imaging data will be acquired at the Douglas Institute site to avoid known issues of scan-site variability (Hainline et al., 2018). Based on our experience collecting fMRI data with geriatric patients, we have allotted 60 min scan-time for each assessment (including setup).

##### Hippocampal volume

T1 weighted MPRAGE will be acquired (TE/TR = 2.98 ms/2,300 ms, TI = 900 ms, α = 9°, FOV = 256 x 240 x 192 mm, GRAPPA of 2, 5 min). Volumetry of the hippocampus and its subfields will be identified using the MAGeT Brain algorithm (Chakravarty et al., 2013; Pipitone et al., 2014). MAGeT Brain improves segmentation over traditional model-based techniques by bootstrapping the segmentation and provides surface-based morphology measures. Cortical thickness will be derived using CIVET version 2.1; (Ad-Dab'bagh et al., 2006) T1-weighted images are pre-processed, tissue classified, white and gray matter surface extracted, and thickness measures are blurred using a 20-mm surface-based kernel.

